### Plans for collection, laboratory evaluation and storage of biological specimens for genetic or molecular analysis in this trial/future use {33}

No genetic or molecular analysis is planned as part of this study. However, informed consent will separately be obtained for the future use of samples, including for genetic analysis. Failure to provide such consent will not preclude participation in this trial.

## Statistical methods

### Statistical methods for primary and secondary outcomes {20a}

Full details of the statistical methods to be employed are found in the statistical analysis plan for the trial. All analysis will be descriptive. Baseline demographic and anthropometric data as well as the defined safety and immunogenicity outcome measures will be tabulated by cohort and group with appropriate measures of spread.

### Interim analyses {21b}

A report describing the safety data to day 14 post-study product administration for the adult and toddler cohorts will be prepared for review by the independent DMC by a statistician allocated to this role but not otherwise involved in the analysis of the trial. The data stratified by group will be available to the DMC members alone and will be reviewed in a closed session of the committee.

The following will prompt a pause to further recruitment and study product administration pending a formal unblinded safety review by the DMC:Any SUSARAny death in a trial participant related to study product administrationAny grade > 3 solicited local AEAny grade > 3 solicited systemic AE or grade > 3 clinical laboratory abnormality judged related to vaccinationThe occurrence of the same grade > 2 solicited systemic AE event or grade > 2 clinical laboratory abnormality judged to be related to vaccination in 20% or more of participants (based on the number of participants dosed at any given timepoint)

The trial could be terminated based on the occurrence of the above safety events or based on the planned day 14 review of the safety data for each cohort. If the DMC did not feel either further dosing within the cohort or age de-escalation respectively was supported by the accumulating safety data, their advice would be provided to the sponsor who would make the ultimate decision in discussion with the investigators and other external experts if judged warranted. However, it is unlikely the sponsor would not follow the advice of the DMC

No interim analysis of immunogenicity data will be performed.

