#### Potential risks and benefits

#### Known potential risks

The safety profile of the MRV when administered by the SC route is well established. The vaccine in the MRV-MNP is the same vaccine, manufactured by the Serum Institute of India Pvt Ltd, that children in The Gambia and in many other countries across the world already receive. Local reactions at the site of injection are common and mild fever and/or rash occur in a small proportion of participants following the measles component of the vaccine but are self-limiting. Transient arthralgia or arthritis is not uncommon in rubella-naïve adolescent and adult females following the rubella component of the vaccine. Low-grade fever and rash are also common following rubella vaccination and are self-limiting. More serious reactions following the SC-administered vaccine are rare.

Human data on both a PLA-MNP and on the IIV-MNP, as well as data from animal models including non-human primates on measles vaccine MNP and MRV-MNP, support the safety of the alternative administration method. The patches themselves are composed of pharmacologically inactive excipients listed in the US Food and Drug Administration’s (FDA’s) Inactive Ingredient Database for Approved Drug Products and are already used in parenteral medications. As such, they are not in themselves expected to significantly alter the safety profile of the MRV. Local AE following MNP-based vaccine administration tends to be more frequent than following N&S-based administration but is mild and self-limiting. No significant differences in the occurrence of solicited systemic AE or unsolicited safety events were reported following IIV-MNP compared to either placebo MNP or IIV delivered by the IM route.

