### Trial design {8}

This is a phase 1/2, single-centre, double-blind, double-dummy, randomized, active-controlled, age de-escalation trial.

All participants will receive either the MRV-MNP and a placebo (0.9% sodium chloride) SC injection (PLA-SC) or a placebo-microneedle patch (PLA-MNP) and MRV by the SC route (MRV-SC). Only those study staff randomizing participants and preparing the study products for administration will be aware of the group to which a participant belongs. Those administering the study products, all other trial staff collecting safety and immunogenicity endpoints, and the participants and parents will be blind.

Decision regarding age de-escalation will be based on a review of the safety data from the preceding cohort (adults for toddlers and toddlers for infants) up to day 14 post-study product administration by an independent data monitoring committee (DMC).

In all, 45 adults (18 to 40 years of age) will be randomized in a 2:1 ratio. Thus, 30 adults will receive MRV-MNP and PLA-SC and 15 adults will receive MRV-SC and PLA-MNP. A total of 120 toddlers (15 to 18 months of age) will be randomized in a 1:1 ratio. Thus, 60 toddlers will receive MRV-MNP and PLA-SC while the same number of toddlers will receive MRV-SC and PLA-MNP. A total of 120 infants (9 to 10 months) will also be randomized in a 1:1 ratio. Thus, 60 infants will receive MRV-MNP and PLA-SC while the same number of infants will receive MRV-SC and PLA-MNP.

Solicited local and systemic adverse events (AEs) will be collected daily from all participants from the day of study product administration to day 13 post-study product administration. Unsolicited AE and serious adverse events (SAEs) will be collected from the day of study product administration to day 180 post-study product administration. All participants will have laboratory investigations (human immunodeficiency virus [HIV], hepatitis B, hepatitis C, haematology and biochemistry) conducted as part of screening. Adults will have safety laboratory investigations repeated on day 7 and day 14 post-study product administration. Toddlers and infants will have safety laboratory investigations repeated on day 7 post-study product administration only. All cohorts could have further laboratory investigations undertaken as clinically indicated.

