## Interventions

### Explanation for the choice of comparators {6b}

The trial will compare the administration of the MRV by MNP to the administration of the same vaccine by SC injection. In both cases, the MRV is manufactured by the Serum Institute of India Pvt. Ltd. The vaccine is licensed for SC injection under the Central Drugs Standard Control Organization of India and pre-qualified by the WHO for supply through UNICEF and other UN agencies. The vaccine meets the requirements of the WHO when tested by the methods outlined in WHO TRS 840 (1994).

To minimize the risk of bias in the safety or other data collected, the trial is of a double-dummy design meaning that all participants receive both an MNP and a SC injection. Participants who receive the MRV via the MNP receive a SC placebo injection (0.9% (weight/volume) sodium chloride). Participants who receive the MRV via SC injection receive a PLA-MNP. Neither the participants, nor the trial staff administering the MNP and SC injections, nor any staff involved in safety or other data collection will therefore be aware of the group to which an individual belongs. Given the importance of ensuring the safety data are robust, as this is the first use of the MRV-MNP in humans, this approach was felt to be warranted. As the MNP application is expected to cause little or no discomfort, the approach was also judged to be warranted in toddlers and infants who will therefore only get the one SC injection as per the normal EPI schedule.

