#### Solicited adverse events

The following solicited local and systemic adverse events will be collected and graded for severity based on the National Institute of Health (NIH), Division of AIDS (DAIDS) Table for Grading the Severity of Adult and Pediatric adverse events (version 2.1. Jul 2017):Adult local: pain, redness/erythema, swelling/induration, pruritisToddler and infant local: pain, redness/erythema, swelling/indurationAdult systemic: acute allergic reactions (day 0 only), axillary temperature, vomiting, diarrhoea, headache, fatigue, myalgia, arthralgia and rashToddler and infant systemic: acute allergic reactions (day 0 only), axillary temperature, vomiting, diarrhoea, irritability, drowsiness, appetite and rash

Solicited AE will be recorded on the day of study product administration (visit 1 — day 0) by the study clinician and daily through home visits conducted by trained field workers between day 1 and day 13 post-study product administration. Any local and systemic AE ongoing after day 13 will be recorded by the study clinician as an unsolicited AE at the day 14 clinic visit (visit 3). Any grade 3 solicited AE identified during home visits will prompt an unscheduled clinic visit and review by a clinical study clinician on the same day or within 24 h at the latest.

Solicited AE data from home visits will be reviewed daily by a study clinician. In addition, home visits will be spot checked by senior members of the field team to ensure the quality and consistency of findings.

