### Composition of the data monitoring committee, its role and reporting structure {21a}

The DMC for the trial will be constituted of four members, all of whom will be independent of both the sponsor and investigator. The DMC will include three members with combined expertise in adult and paediatric medicine, clinical vaccine trials, MNP technology and clinical research in LMIC in sub-Saharan Africa, as well as an independent DMC statistician.

The DMC will review all safety data, and data on protocol adherence, to day 14 following study product administration in the adult and subsequently the toddler cohort and provide advice to the sponsor on whether age de-escalation should continue as planned. The DMC will also meet if a pause rule is met during trial conduct and will recommend any additional measures to the sponsor judged to be required. Full details of the DMC’s function and workings are provided in the DMC charter.

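### As printed, repeated non-serious grade 3 local reactions meet no rule that pauses dosing within a cohort

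*Protocol article*

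**What the plan says.** Interim analyses {21b} lists five events that pause recruitment and dosing until the data monitoring committee (DMC) has reviewed unblinded safety data:

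1. any suspected unexpected serious adverse reaction (SUSAR);
2. any related death;
3. any solicited local event above grade 3;
4. any related solicited systemic event or laboratory abnormality above grade 3;
5. a repeated-event clause for "the same grade > 2 solicited systemic AE event or grade > 2 clinical laboratory abnormality", if judged related and seen in at least 20% of participants, "based on the number of participants dosed at any given timepoint".

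Local reactions appear only in the third item.

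Other safeguards are described elsewhere. Under Solicited adverse events, "Any grade 3 solicited AE identified during home visits will prompt an unscheduled clinic visit", with clinician review within 24 hours at the latest, and a clinician looks at home-visit data daily. Known potential risks describes a sentinel group and a slow start in children. Under Trial design {8}, "Decision regarding age de-escalation will be based on a review of the safety data from the preceding cohort". The section on the DMC's composition and role says that it reviews safety data "to day 14 following study product administration in the adult and subsequently the toddler cohort", and that full details of its "function and workings are provided in the DMC charter". The charter is not among the documents available.

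**The concern.** The protocol justifies its blinding "as this is the first use of the MRV-MNP in humans". The local site is where the patch is expected to differ from the injection: "Local AE following MNP-based vaccine administration tends to be more frequent than following N&S-based administration but is mild and self-limiting". Repeated grade 3 local reactions would contradict that expectation, yet they are the one class of repeated grade 3 solicited event with no pause rule. Attribution cannot explain the omission, because the Causality section treats solicited local reactions as related by definition.

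The exposure lies within a cohort. Up to 30 adults or 60 toddlers could receive the measles and rubella vaccine by microneedle patch (MRV-MNP) before the DMC sees such reactions at its planned day 14 review. Site assessors are blinded, so clinicians who see individual cases cannot tell a vaccine-patch effect from a placebo-patch effect.

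**Working it through.** The plan states no operating characteristics for its pause rules, so there is no figure of its own to reproduce. All event rates below are assumptions; the document gives no grade 3 local rate for the MRV-MNP.

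**Step 1. Apply the five rules to a non-serious grade 3 local reaction.**
- SUSAR: needs a serious or important medical event that is also related and unexpected. Grade and repetition do not suffice.
- Related death: no.
- Local event above grade 3: 3 > 3 is false.
- Single systemic or laboratory event: wrong type.
- Repeated-event clause: 3 > 2 is true, but local events are not named.

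None is met, whether the count is 1 or 45 of 45 adults, or 120 of 120 toddlers. For a related systemic or laboratory event of the same grade, the clause is met at 0.20 × 45 = 9 adults or 0.20 × 120 = 24 toddlers or infants (full cohort; a per-cohort denominator is assumed, as the text does not say).

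**Step 2. False pauses if local events of grade 3 or higher joined the clause.** Let k be the number with the same reaction at the same site among the first n dosed. Dosing pauses if k/n ≥ 0.20 at any n from a minimum m to the cohort size N. With independent participants and true rate p, the chance h for one series follows exactly by updating the distribution of k one participant at a time. Toddlers and infants have 3 reactions × 2 sites = 6 series; adults have 4 × 2 = 8. For S independent series the cohort chance is 1 − (1 − h)^S. Example: p = 2%, m = 10, h = 1.70%, so 1 − (1 − 0.0170)^6 = 9.8%.

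| Minimum dosed | h at p = 1 / 2 / 5% | Toddlers or infants, 6 series, N = 120 | Adults, 8 series, N = 45 |
|---|---|---|---|
| None | 5.0 / 10.0 / 25.0% | 26.5 / 46.9 / 82.2% | 33.7 / 57.0 / 90.0% |
| 10 | 0.44 / 1.70 / 9.73% | 2.6 / 9.8 / 45.9% | 3.4 / 12.8 / 55.9% |
| 20 | 0.004 / 0.063 / 1.83% | 0.03 / 0.38 / 10.5% | 0.04 / 0.51 / 13.7% |

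A minimum is needed because one event among the first five dosed is already 20%. Correlation between series would lower the cohort figures.

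**Step 3. Chance that the extended clause pauses dosing on a real signal.** Suppose one reaction type occurs only at the patch site in the MRV-MNP arm. Treating allocation as independent, p is the arm rate × 1/2 in toddlers or infants (1:1) and × 2/3 in adults (2:1).

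| Arm rate | Toddlers or infants, minimum 10 | Toddlers or infants, minimum 20 | Adults, minimum 10 | Adults, minimum 20 |
|---|---|---|---|---|
| 10% | 9.7% | 1.8% | 16.5% | 4.8% |
| 20% | 33.6% | 17.5% | 52.2% | 36.2% |
| 30% | 64.5% | 51.8% | 83.1% | 75.5% |
| 40% | 89.7% | 85.5% | 96.5% | 94.7% |

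With the rules as printed, every cell is 0%. At full enrolment in a toddler or infant cohort the clause needs 24 events, and 24/60 = 40% of the MRV-MNP arm, so it is insensitive late in dosing.

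**Step 4. What the existing reviews would see.** Before infants are dosed, the DMC has day 14 data on 30 + 60 = 90 MRV-MNP recipients. The chance of at least one case among them is 1 − 0.95^90 = 99.0% at a 5% rate and 1 − 0.98^90 = 83.8% at 2%, if rates are similar across ages. This measures the protection that infants already have, not the gap.

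**The case against.** **The sign may be a misprint.** Exclusion criteria uses both > and ≥ for the same 37.5°C threshold. Read with ≥ throughout, the pause rules are coherent: any single grade 3 local reaction pauses dosing, and the repeated clause concerns grade 2. Leaving local reactions out of that clause would then be sensible, since 13 of 15 recipients of the placebo patch had grade 2 erythema on day 0. This stands as an open question. Against it, the same section prints ≥ 2 for laboratory toxicity, so the sign was available. Nor is it enough to correct the single-event signs alone, because the > 2 clause would then be redundant for systemic and laboratory events.

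**The choice may be deliberate, and the remedy is weak at plausible rates.** Milder handling of local reactions is defensible. In the influenza patch trial, 1 of 50 patch recipients had a grade 2 or 3 local event, and at a 10% arm rate the extended clause would rarely fire. That limits what the change can achieve. It does not supply a reason for having no repeated-event limit at all.

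**A reader might infer that grade 3 local reactions go unmonitored, or that infants are exposed without oversight.** The documents do not support that. Sentinel data are assessed before recruitment proceeds, children start slowly, and each grade 3 event found at a home visit is reviewed within 24 hours. The DMC sees adult data before toddlers are dosed and toddler data before infants are. A reaction that is serious or an important medical event, and unexpected, can still pause dosing as a SUSAR. Only adult and toddler reports are named, but Interim analyses {21b} also speaks of day 14 review for each cohort, and the charter may hold more.

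**Conclusion.** The gap is real as the text is printed. It is narrow: repeated, non-serious grade 3 solicited local reactions cannot pause dosing within a cohort at any frequency, while related systemic and laboratory events of that grade can at 20%. The other safeguards reduce the consequences but are not pause rules. This is a low-cost improvement to consider, not a defect that makes the trial unsafe.

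The conclusion rests on reading > literally and on the charter adding no further rule. The size of the benefit rests on assumed rates, independent participants and denominators per cohort. On those terms the extended clause is a backstop for arm rates of roughly 30% and above, where it fires in more than half of cohorts for either minimum.

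**What to change.** First, confirm whether the thresholds are meant as > or ≥, and state the grades in words in the pause rules and the DMC charter.

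If they are meant as printed, add to the repeated-event clause: the same solicited local AE of grade 3 or higher in 20% or more of participants dosed in the cohort. Count patch and injection sites separately, and apply the count only after a minimum fixed in advance, for example 10 or 20. No relatedness judgement is needed. Do not extend the clause to grade 2 local reactions: they are expected with the patch and would pause dosing almost at once.

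The data are already collected daily, so the cost is a short amendment and an occasional extra DMC review. With a minimum of 20, the chance of such a review per cohort is about 0.4% to 0.5% at a 2% true rate per reaction and site, and 10% to 14% at 5%. With a minimum of 10 it is about 10% to 13% and 46% to 56%. The lower minimum buys earlier detection, and the choice between them is the sponsor's and the DMC's to make.

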### Methods for additional analyses (e.g. subgroup analyses) {20b}

No additional or subgroup analyses are planned.

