#### Measles and rubella vaccination

In its latest position paper on measles vaccines, the World Health Organization (WHO) recommends that reaching children with two doses of a measles-containing vaccine (MCV) should be standard for all national immunization programs [43]. In addition, it recommends that countries aiming for measles elimination should consistently achieve ≥95% two-dose coverage equitably in children across all districts [43].

In countries with ongoing measles virus transmission, the first dose of a measles-containing vaccine (MCV1) should be given at 9 months of age, following which around 85% of infants will seroconvert. Vaccination at 12 to 15 months of age increases the seroconversion rate to more than 95%, but this later age of administration is only appropriate in non-endemic settings when the risk of exposure to wild-type measles virus before this age is low [8].

In order to achieve the high levels of population immunity necessary to interrupt measles virus transmission, a routine second dose of a measles-containing vaccine (MCV2) is required at either 15 to 18 months of age or at school entry depending on local MCV1 coverage data as well as epidemiological and logistical considerations [43].

In settings with suboptimal routine vaccination coverage, periodic national or sub-national vaccination campaigns (supplementary immunization activities [SIA]) are needed. SIAs are a highly effective strategy to increase measles and rubella population immunity in settings with weak health systems and hence low Expanded Programme on Immunization (EPI) coverage. The timing and target age group for campaigns should be determined based on knowledge of coverage with routine vaccines and previous campaigns, as well as surveillance, and any available seroprevalence data. Based on mathematical models, high coverage campaigns targeting children less than 5 years of age are generally more cost effective than campaigns achieving lower coverage across a wider age range. However, since SIAs will generally be implemented using a combined measles and rubella vaccine, rubella epidemiology and rates of CRS also need to be considered in such planning decisions [44].

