Despite The Gambia having a generally efficient EPI programme, the level of measles vaccine coverage remains considerably below that required to prevent outbreaks without regular national SIAs [59]. Measles and more recently measles and rubella SIAs have consequently been required every 3 to 4 years since 2003 (2003, 2007, 2011, 2013, 2016, due 2020 but now delayed). Based on the most recent Gambian Bureau of Statistics/UNICEF Multiple Indicator Cluster Survey (MICS), published in July 2019, the coverage with a first dose of the MRV by 12 months of age in The Gambia is 82.4%. This rises to 86.8% when children up to 23 months of age are included. The coverage with the recommended second dose of the vaccine at 24 months of age is 64.1%. This only rises to 67.1% including children up to 35 months of age. Therefore, even assuming all children were protected by a single dose of the vaccine, the vaccine-induced immunity in children is considerably below minimum 92% level required to prevent measles outbreaks. Our own published data indicate that only around 80% of Gambian infants will be protected by a single dose of the vaccine [60], suggesting that the 86.8% coverage provided a population immunity level of only around 70% in those cohorts. Reflecting this, the last significant measles outbreak occurred in The Gambia in the first part of 2016. More than 120 cases were officially confirmed. This outbreak was controlled by a national MRV SIA conducted in April of the same year. Further sporadic cases of measles continue to be reported. Indeed, there were at least 12 laboratory-confirmed cases of measles in the Western region of The Gambia in the first quarter of 2020 — reflecting the accumulation of measles-susceptible children since the last campaign in 2016. Some of these cases were in children from neighbouring countries with lower vaccination coverage. This reinforces the critical need to maintain high levels of immunity in the Gambian population if significant outbreaks are to be avoided. The first-dose measles coverage in Senegal is even lower than in The Gambia, being 65.0% and 70.5% at 12 and 24 months of age respectively [61]. Coverage in Guinea-Bissau is similarly low. The additional risk of measles being imported is therefore significant given the movement of the population in the sub-region.

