The same concerns apply to rubella vaccination coverage. In this case, failure to generate adequate immunity in childhood risks a population of women entering their period of childbearing without rubella immunity and being exposed during pregnancy through ongoing low-level virus circulation. Again, our own published data suggest 10% of infants will have been exposed to rubella by 9 months of age. This is supported by ongoing case detection with close to 150 laboratory-confirmed cases being reported before the national SIA in 2016. This is a concern when vaccine-induced immunity is partial, as likely to be the case in The Gambia, meaning that many women are no longer likely to be immune through natural infection in childhood, but that virus circulation is not sufficiently suppressed to reliably prevent women becoming exposed when pregnant. In this case, the risk of CRS can increase despite the vaccine programme [60, 62].

Consequently, The Gambia remains dependent on MRV SIAs, and novel approaches to facilitate campaigns and increase routine coverage while also minimizing the burden on the health sector are highly relevant. The MRV-MNP offer important potential advantages over conventional Needle and Syringe (N&S) administration in both situations.

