A key element to ensure that two-dose MRV coverage attains the levels required for elimination is to ensure that opportunities for vaccination are not missed. However, MRV vaccines are supplied in 10 and 20 dose vials and vaccine wastage is a concern. Therefore, infants and children who are due or overdue this vaccine may be asked to return to future clinics if insufficient numbers are present on a given day. In many parts of The Gambia, outreach clinics, for example to smaller communities, are only conducted monthly. On this basis, MRV will be further delayed, even assuming a parent reattends. The MNP are provided in single-dose packets therefore can be provided to single infants and children without delay or wastage. Consequently, they are expected to facilitate opportunistic vaccination to a degree which is not possible when multidose vials are used.

Generating early data on the MRV-MNP in this setting is appropriate and will minimize the timeline for MRV-MNP development. Serological data from a population of adults recruited based on comparable inclusion and exclusion criteria to those to be used in this trial suggest that the baseline measles-specific SNA titres and rubella-specific IgG concentrations are likely to be high. This is expected to limit the insights regarding the immunogenicity of the vaccine in this group. For this reason, age de-escalation to the future target toddler and infant age groups, based on the safety data from the preceding cohort, is seen as fundamental to gaining the information required on both the safety and immunogenicity of MRV-MNP to base key product development decisions. Fifteen to 18-month-old toddlers are the target age group for MCV2, while 9-month-old infants are the target age group for MCV1 based on current WHO recommendations [43].

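### With subgroup analyses ruled out, toddler measles seroprotection is pooled over baseline immunity, which strongly dilutes any difference between patch and SC injection

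*Protocol article*

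**What the plan says.** All references are to the protocol article.

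- Section {20b} reads "No additional or subgroup analyses are planned". Section {20a} refers to the statistical analysis plan for detail and describes tabulation by cohort and group.
- Outcomes {12} for adults and toddlers includes the percentage seroprotected at day 42 and day 180, with no condition on baseline status. It also lists two endpoints measured against baseline: the geometric mean fold rise (GMFR) to day 42, and the percentage with seroconversion or a four-fold rise to day 42.
- The inclusion criteria in {10} require toddlers to have had a parenteral measles and rubella vaccine at 9 to 12 months.
- Trial rationale and relevance to The Gambia says, in a paragraph on measles, that "only around 80% of Gambian infants will be protected by a single dose of the vaccine". Measles and rubella vaccination says the first measles dose "should be given at 9 months of age, following which around 85% of infants will seroconvert".
- Trial design {8} says "A total of 120 toddlers (15 to 18 months of age) will be randomized in a 1:1 ratio", so 60 per arm. It also has baseline serology measured in everyone.
- Section {18a} sets the thresholds at above 120 mIU/mL for measles and above 10 IU/mL for rubella.
- For adults, the rationale says that "the baseline measles-specific SNA titres and rubella-specific IgG concentrations are likely to be high" and adds: "This is expected to limit the insights regarding the immunogenicity of the vaccine in this group".

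**The concern.** A toddler already above the measles threshold on the day of dosing will normally still be above it at day 42, whatever the patch delivers. On the article's own figures most toddlers are expected to be in that position. The pooled seroprotection percentage in each arm is therefore largely a measure of the earlier dose, and only the minority who start seronegative carry information on whether the new dose protects.

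The response endpoint refers to baseline but pools two events: crossing the threshold, which only a seronegative child can do, and a four-fold rise, which is what a seropositive child must show. Both pooled figures shrink a real difference between patch and SC.

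The article draws this consequence of high baseline immunity for adults but does not carry it over to primed toddlers. The trial is meant to supply data for go/no-go decisions, judged on whether patch responses are comparable with SC. A small pooled gap reads very differently from a large gap in the children whose first dose failed.

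**Working it through.** **Inputs**

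| Input | Value | Source |
|---|---|---|
| Toddlers per arm | 60 | Trial design {8} |
| Measles protection after one dose | about 80% | Trial rationale |
| Seroconversion after a 9-month dose | about 85% | Measles and rubella vaccination |
| Share protected at toddler baseline, b | 0.80, range 0.70 to 0.85 | assumption, from the two rows above |
| Seronegatives converted by SC | 95% | assumption |
| Seronegatives converted by the patch | 50% (partly failing) or 0% (inert) | assumption |

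All intervals are two-sided 95%. Single proportions use the Wilson score method and differences (patch minus SC) use Newcombe's method built from Wilson limits.

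**1. The article's own figure.** Table 4 gives 80.0% (68.2 to 88.2) for n = 60. The Wilson interval for 48/60 is 68.2 to 88.2, so the method matches.

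**2. Pooled seroprotection.** For conversion s among seronegatives, and no loss of protection among seropositives, the expected percentage is b + (1 - b) × s. With b = 0.80:

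- SC: 0.80 + 0.20 × 0.95 = 99%
- Partly failing patch: 0.80 + 0.20 × 0.50 = 90%
- Inert patch: 0.80 + 0.20 × 0 = 80%

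**3. Partly failing patch against SC, pooled.** 90% - 99% = -9 points, CI -19.2 to -0.4 on expected percentages. In whole counts, 54/60 v 59/60 is -8.3 points, CI -18.6 to +0.6.

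**4. The same comparison among seronegatives.** 60 × 0.20 = 12 are expected per arm. 50% - 95% = -45 points, CI -70.0 to -9.0. In whole counts, 6/12 v 11/12 is -41.7 points, CI -67.2 to -5.1. The pooled gap is the seronegative gap multiplied by (1 - b): 45 × 0.20 = 9.

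**5. The response endpoint.** If no seropositive child has a four-fold rise, the response is (1 - b) × s: 0.20 × 0.50 = 10% for the patch and 0.20 × 0.95 = 19% for SC, CI for the difference -21.8 to +3.9. If 20% of seropositive children in both arms have a four-fold rise, add 0.80 × 0.20 = 16 points to each arm: 26% v 35%, CI -24.8 to +7.4.

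**6. Other baseline shares, partly failing patch**

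| b | Patch | SC | Pooled gap (points) | Seronegatives per arm |
|---|---|---|---|---|
| 0.70 | 85.0% | 98.5% | 13.5 | 18 |
| 0.80 | 90.0% | 99.0% | 9.0 | 12 |
| 0.85 | 92.5% | 99.25% | 6.75 | 9 |

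At b = 0.85 the pooled CI is -16.3 to +1.2. The gap among seronegatives is 45 points in every row.

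**7. Fully inert patch.** Pooled seroprotection is 80% v 99%, a difference of -19 points, CI -30.8 to -8.4. The same patch would show a GMFR of about 1 and about 0/60 responders (Wilson CI 0 to 6.0%).

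**The case against.** A reader might infer that an inert patch could pass as comparable with SC because its arm would still show about 80% seroprotection. The documents do not support that. There is a randomised SC arm, and step 7 shows the difference would be plain. GMFR and the response endpoint are already planned and refer to baseline, and 120 infants who have never had the vaccine, 60 per arm, are a better test of primary response than a handful of seronegative toddlers. Randomisation also balances carried-over immunity in expectation, so it dilutes the contrast and does not create false comparability. On expected percentages, even the pooled interval for the partly failing patch just excludes zero. All of this stands.

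It does not remove the dilution. The response endpoint shrinks the same signal (step 5), GMFR averages over both serostatus groups, and the infants do not show what the patch does for toddlers whose first dose failed.

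Two further readings go too far. One is that nearly all adults start seroprotected: the article gives no percentage, says only that baseline levels are likely to be high, and openly states the limit this sets. The other is to treat 80% as a measured toddler baseline or as a rubella figure: it is protection of infants after one dose, given in a measles context. The remark that "10% of infants will have been exposed to rubella by 9 months of age" concerns exposure in infants and is at most a minor matter here.

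It is also fair to say that the trial is descriptive, that immunogenicity is secondary and that no data are lost, since baseline serology is collected. The analysis plan is not at hand, but {20b} is an express exclusion and not a detail left to that plan.

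**Conclusion.** The point holds as one of reduced sensitivity and interpretability, chiefly for measles in toddlers. It is not an inability to detect failure. In the worked example a 45-point deficit among seronegative toddlers appears as 9 points in the pooled figure, and as 6.75 to 13.5 points if 85% to 70% are protected at baseline. In whole counts the pooled interval at 80% includes zero, while the seronegative interval does not.

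This rests on three assumptions: that the one-dose share of about 80 to 85% roughly carries through to 15 to 18 months, although waning and natural boosting are not quantified; that SC converts 95% of the remainder; and that the patch converts half of them. The dilution factor depends only on the first. The change is worth making before unblinding because it is cheap and avoids a split chosen after the results are seen.

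**What to change.** Amend {20b}, and align the analysis plan, to prespecify the following by cohort and group with 95% CIs, chiefly for toddlers:

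- in participants seronegative at baseline (measles at or below 120 mIU/mL; rubella at or below 10 IU/mL, each antigen classified separately): seroconversion, and seroprotection at day 42 and day 180;
- in participants seropositive at baseline: four-fold rise and GMFR to day 42.

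Keep the existing overall percentages alongside.

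The cost is extra tables from samples and thresholds already in the protocol. The drawback is size: about 9 to 18 seronegative toddlers per arm for measles, with wide intervals. At 12 per arm, 0/12 has a Wilson upper limit of 24.2% and 12/12 a lower limit of 75.8%, so the stratum is small but still informative. The tables should be labelled descriptive.
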